#### Secondary outcomes

*PNF*: The number of patients experiencing PNF in each arm will be compared using Fisher's exact text. The cause of graft loss will be tabulated by arm. The duration of DGF in days will be summarised using the Kaplan-Meier estimate of the duration of DGF for all those who experienced DGF and compared using a log-rank test.

*Outcome measures*: The number of patients that experience functional DGF will be compared using Fisher's exact test. The CRR2 and CRR5 will be compared by arm using a two-sample t-test. The length of hospital stay, defined from admission to discharge, will be estimated using the Kaplan-Meier method, with deaths in hospital censored, and compared between arms using the log-rank test.

*Biopsy-proven acute rejection rate*: The number of patients in each arm will be compared using Fisher's exact test. Longitudinal changes in serum creatinine and eGFR will be separately assessed at 1, 3, 6 and 12 months post-transplant and mean values compared using two-way analysis of variance with repeated measures for patients in each arm of the trial. Any difference between arms in the way serum creatinine and eGFR change over time will also be assessed using this model. Patient survival (time from transplant to death) and allograft survival (time from transplant to graft loss or return to dialysis) will be analysed using a Kaplan-Meier estimate of the probability of an event after 12 months and a log-rank test. Time to graft loss or return to dialysis will be modelled.

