#### Secondary outcome measures

The secondary outcome measures include incidences of primary non-function (PNF) defined as the permanent lack of allograft function from the time of transplantation (This will include graft losses due to irreversible rejection and vascular thrombosis. The cause of graft loss will be recorded.); the duration of DGF in days; functional DGF (fDGF) defined as <10% fall in serum creatinine for 3 consecutive days in the first week post-transplant; creatinine reduction ratio day 2 (CRR2=creatinine day 1−creatinine day 2/creatinine day 1) and CRR5 (CRR5=pretransplant creatinine−creatinine day 5/pretransplant creatinine);^19^ length of hospital stay, rates of biopsy-proven acute rejection rate and measures of renal function (serum creatinine and estimated glomerular filtration rate (eGFR)) at 1, 3, 6 and 12 months post-transplant. Patient survival (time from transplant to death) and allograft survival (time from transplant to graft loss or return to dialysis) will be recorded. The EVNP score will be calculated for each kidney undergoing EVNP (table 1). The predictive value of this assessment score on graft function and outcome will be evaluated. A clinical decision on the suitability of the kidney for transplantation will be made using normal criteria prior to perfusion. However, the EVNP assessment score will be taken into consideration. Arterial and venous samples will be collected during perfusion and used to measure oxygen consumption, acid–base balance and concentrations of sodium, potassium, glucose, lactate and calcium. Concentrations of sodium and potassium will also be measured in the urine at the end of EVNP.

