### Statistics

#### Sample size determination

The trial size was calculated with respect to the primary end point, which is DGF defined as the requirement for dialysis in the first 7 days post-transplantation. Based on 5 years of data from the three participating centres, the overall rate of DGF in DCD kidney transplants is 50%. In a pilot series of kidney transplants from extended criteria donors (ECD), 18 kidneys undergoing CS followed by 1 hour of EVNP were compared with a historical control group of 47 ECD transplants after CS alone. The DGF rates were 1/18 (6%) in the EVNP group compared with 17/47 (36%) in the CS group.^14^

Using a fixed sample size study, with interim analyses after 125 and 250 patients have been enrolled and reached 365 days post-transplant, a total of 376 patients receiving a DCD kidney (Maastricht categories III and IV controlled donors) will be required to detect a 30% relative reduction in DGF (from 50% to 35%) with a power of 80% and a statistical significance of α=0.05. To allow for a study withdrawal rate of 6%, a total of 400 patients will be recruited.

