#### Primary analysis

The number of patients who experience DGF between the two groups will be compared using a logistic regression model adjusting for cold ischaemic time and donor age.

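### Functional DGF gets an unadjusted Fisher's exact test while DGF gets an adjusted logistic model: valid, but less efficient and not directly comparable with the primary result

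*Protocol article*

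**What the plan says.** The Primary analysis section of the article has the number of patients with DGF "compared using a logistic regression model adjusting for cold ischaemic time and donor age". DGF means dialysis within 7 days of transplant.

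The Secondary outcome measures section lists "functional DGF (fDGF) defined as <10% fall in serum creatinine for 3 consecutive days in the first week post-transplant", which covers the same week. For its analysis, the Secondary outcomes section states "The number of patients that experience functional DGF will be compared using Fisher's exact test" and names no covariates. Biopsy-proven acute rejection is treated alike: "The number of patients in each arm will be compared using Fisher's exact test". Primary non-function also gets Fisher's test. The t-tests and log-rank tests for the other secondary outcomes are likewise described without covariates.

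The sample size rests on the primary outcome alone: "a total of 376 patients receiving a DCD kidney" for a fall in DGF from 50% to 35%, "with a power of 80% and a statistical significance of α=0.05". No power is claimed for any secondary outcome, and no expected rate is given for functional DGF or rejection. The article calls its analysis section a summary, with a full statistical analysis plan to follow before the first interim analysis. The test for functional DGF is nevertheless named, not left open.

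**The concern.** DGF and functional DGF are two binary readings of early graft function over the same seven days, one from dialysis and one from creatinine. The article concedes under its strengths and limitations that dialysis-defined DGF is subjective, and the trial is open-label. Readers will therefore set the two results side by side. As planned, one will be an adjusted odds ratio and the other an unadjusted exact p-value.

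Three things follow.

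- Fisher's test works on a discrete conditional distribution, so its actual size is below the nominal 5% and some power is given up.
- The plan treats donor age and cold ischaemic time as worth adjusting for in early graft function, then drops them for the sister outcome without giving a reason.
- An adjusted odds ratio from a logistic model is conditional on its covariates. It differs from a crude one even when the arms are balanced, so part of any gap between the two results could come from method alone.

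At stake are efficiency and comparability. The false-positive rate is not at risk.

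**Working it through.** **Inputs.** From the article: 1:1 allocation, 376 evaluable patients (188 per arm), 400 recruited, 6% withdrawal, 50% versus 35%, alpha 0.05 (taken as two-sided), 80% power. Assumed: event rates for functional DGF and rejection, and the prognostic strength of the covariates. The calculations treat patients as independent and ignore the interim looks.

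**1. The plan's own figure.** n per arm = [1.960·√(2·0.425·0.575) + 0.842·√(0.5·0.5 + 0.35·0.65)]² / 0.15² ≈ 170, or 340 in total. With continuity correction it is 183 per arm, or 366, within 3% of 376. Exact Fisher power also first reaches 80% at 366 (80.3%). Withdrawal: 376 / 0.94 = 400, which reproduces exactly.

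**2. Fisher's size and power by full enumeration.** With n = 188 per arm, the rejection probability is the sum over all x and y of Bin(x; n, p1)·Bin(y; n, p2), counted where the test gives p ≤ 0.05. Setting p1 = p2 gives the size.

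| Event rate | Fisher size | Chi-squared size |
|---|---|---|
| 50% | 4.4% | 5.2% |
| 30% | 3.9% | 5.0% |
| 20% | 3.7% | 5.0% |
| 15% | 3.6% | 5.0% |
| 10% | 3.3% | 5.0% |

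| Comparison | Fisher power | Chi-squared power | Gap (points) |
|---|---|---|---|
| 50% v 35% | 82.1% | 84.7% | 2.6 |
| 20% v 10% | 74.1% | 78.3% | 4.2 |
| 15% v 7.5% | 57.7% | 64.3% | 6.6 |
| 10% v 5% | 37.9% | 45.9% | 8.0 |

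**3. Adding the covariates, by simulation.** Two covariates were used, with 3,000 trials per row and 188 per arm. Marginal rates were held at 50% v 35%. Strength is the standard deviation of the covariates' joint contribution on the log-odds scale.

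| Strength | Fisher | Adjusted logistic | Gap (points) |
|---|---|---|---|
| 0 | 81.8% | 83.7% | 1.9 |
| 0.3 | 81.9% | 84.2% | 2.3 |
| 0.5 | 82.7% | 86.3% | 3.6 |
| 0.7 | 82.2% | 87.9% | 5.7 |
| 1.0 | 82.0% | 89.7% | 7.7 |

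The simulation error of each power is about √(0.84·0.16/3000) = 0.7 points. Simulated type I error of the adjusted model at a 50% rate was 4.8% to 5.7% across the rows, with an error of about √(0.05·0.95/3000) = 0.4 points. A second, separate simulation gave about 84% to 89% for the adjusted model against 83% for Fisher, with type I error about 4.5%. The gap at the strong end is thus about 6 to 8 points.

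**4. A less common outcome.** At 15% v 7.5%, the same simulation gave 64.1% v 58.3% with no covariate effect (gap 5.8) and 66.3% v 57.2% at strength 1.0 (gap 9.1). At such rates most of the gain comes from leaving Fisher's test, not from the covariates.

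**The case against.** The case for leaving the plan alone is respectable.

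- Fisher's test is valid in a randomised comparison and holds type I error at or below 5%. Nothing in the article contradicts its use, and no promised power is lost.
- An adjusted primary analysis with simple unadjusted secondary ones is a common and coherent design.
- At 50% v 35%, Fisher still has 82.1% power with 376 patients and 83.5% with 400.
- Part of the gap to chi-squared is level, not efficiency, since chi-squared runs at 5.2% when the event rate is 50%.
- The unseen statistical analysis plan may add adjusted estimates.

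All of this stands, and it limits the point to an improvement. It does not remove it: the article names the weaker method for functional DGF, and a better one uses data that the primary model already requires.

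Four stronger readings are tempting but unsupported.

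- A reader might infer that the choice of test is an error. It is not.
- A reader might take functional DGF to be the designated main check on a subjective primary outcome. The article says only that the secondary outcomes include more sensitive measures of renal function, in the plural.
- A reader might extend the argument to rejection with equal force. That turns on an event rate the article does not give. Where events are few, Fisher's test is the conventional choice.
- A reader might simply copy the primary model. Randomisation follows arrival of the kidney at the centre, and perfused kidneys go back on ice until implanted. Total cold ischaemic time may therefore not be fixed at randomisation.

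**Conclusion.** The point holds as an optional gain in efficiency and comparability for functional DGF. Fisher's test is conservative at this sample size. Against an adjusted logistic model, at 50% v 35%, it costs about 2 points of power if the covariates carry no information and about 6 to 8 if they are strongly prognostic. This assumes that functional DGF is about as common as DGF. Neither that rate nor the covariates' strength is in the article, so the range should be quoted and not a single value. The lack of an effect estimate comparable with the primary odds ratio does not depend on those assumptions. For rejection the point is conditional on enough events, and for primary non-function there is no objection to Fisher's test.

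**What to change.** In the statistical analysis plan:

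- Analyse functional DGF by logistic regression on treatment arm, adjusted for donor age and for cold ischaemic time measured up to randomisation. Report the adjusted odds ratio with its 95% confidence interval.
- State the definition of cold ischaemic time once and use it in both the DGF and functional DGF models. Otherwise the two estimates will still not be on the same footing.
- Use this model for biopsy-proven acute rejection only if events reach a minimum number fixed in advance.
- Keep Fisher's exact test for primary non-function, and name it as the fallback for any outcome with too few events.

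The cost is a few sentences, and the article places the writing of that plan before the first interim analysis. The primary model already needs donor age and cold ischaemic time. The only further item is the time of randomisation, which a web-based system can be expected to log (an assumption). Sample size, visits and conduct do not change.

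### CRR5, a proportional change from pretransplant creatinine, is compared by an unadjusted t-test, which loses precision whenever CRR5 stays correlated with that baseline

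*Protocol article*

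**What the plan says.** Under Secondary outcome measures, the protocol article gives the definition "CRR5=pretransplant creatinine−creatinine day 5/pretransplant creatinine". It is printed without brackets, but the name and the context make it a proportional fall: (pretransplant − day 5) / pretransplant. The companion measure is "CRR2=creatinine day 1−creatinine day 2/creatinine day 1".

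Under Secondary outcomes in the analysis section, both are given one test: "The CRR2 and CRR5 will be compared by arm using a two-sample t-test". No covariate is named for CRR5 anywhere in the article. Adjustment for baseline factors is described only for DGF, in the Primary analysis, which uses a "logistic regression model adjusting for cold ischaemic time and donor age".

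The sample size is justified for DGF alone. No SD, target difference or power is stated for CRR5.

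**The concern.** Every CRR5 value needs a pretransplant creatinine, so the baseline is already in hand, but it enters only as a divisor. A ratio to baseline is free of the baseline only under a particular relation between the two measurements, and nothing in the article suggests that this relation holds. Otherwise part of the spread in CRR5 is explained by pretransplant creatinine, and an unadjusted test leaves that part in the error term. A chance difference between arms in mean pretransplant creatinine then also shifts the estimated effect.

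This matters because the article concedes that dialysis-defined DGF is subjective and that the trial is unblinded. It presents the week-one function measures as more sensitive. CRR5 is a laboratory measure in that group, so its precision is worth having.

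**Working it through.** **The plan's own figure.** For DGF of 50% v 35%, two-sided α 0.05 (sidedness assumed) and 80% power:

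n = [1.96·√(2·0.425·0.575) + 0.8416·√(0.5·0.5 + 0.35·0.65)]² / 0.15² = 169.3, so 170 per arm (340 in total).

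The continuity correction gives 183 per arm (366), within 3% of "a total of 376 patients receiving a DCD kidney". Then 376 / (1 − 0.06) = 400, as stated. These figures concern DGF and do not depend on how CRR5 is tested. They supply the 376 / 2 = 188 per arm used below.

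**What a covariate does.** If r is the within-arm correlation of CRR5 with the covariate, adjustment multiplies the error variance by 1 − r². Suppose the t-test had 80% power. Adjusted power is Φ(2.8016/√(1 − r²) − 1.96), and the N giving the same precision is 376·(1 − r²):

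| r | adjusted power | equivalent N |
|---|---|---|
| 0 | 80.0% | 376 |
| 0.2 | 81.6% | 361 |
| 0.3 | 83.6% | 342 |
| 0.4 | 86.4% | 316 |
| 0.5 | 89.9% | 282 |
| 0.6 | 93.8% | 241 |

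**What r might be.** The documents give no value. Assume log-normal creatinine with log-scale SDs s0 (pretransplant) and s5 (day 5) and correlation ρ between them. The log ratio has variance v = s0² + s5² − 2ρ·s0·s5, and

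r(CRR5, log baseline) = (s0 − ρ·s5) / √(e^v − 1).

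So r is zero exactly when ρ·s5 = s0, positive when ρ·s5 is smaller, and negative when it is larger. For example:

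- (ρ, s0, s5) = (0.5, 0.4, 0.4): v = 0.16, r = 0.2 / 0.4165 = 0.48.
- (0.5, 0.35, 0.7): ρ·s5 = 0.35 = s0, so r = 0.
- (0.7, 0.4, 0.7): v = 0.258, r = −0.09 / 0.5425 = −0.17.

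**Power on CRR5 itself.** The effect is set so that a regression of log day-5 creatinine on arm and log baseline has about 80% power. The t-test column is simulated (188 per arm). The adjusted column applies Φ((z + 1.96)/√(1 − r²) − 1.96), where z is the normal quantile of the t-test power.

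| ρ, s0, s5 | r | t-test on CRR5 | CRR5 adjusted for log baseline | gain (points) |
|---|---|---|---|---|
| 0, 0.4, 0.4 | 0.65 | 45.0% | 67.6% | 22.6 |
| 0.5, 0.4, 0.4 | 0.48 | 64.5% | 75.7% | 11.2 |
| 0.7, 0.4, 0.4 | 0.38 | 71.1% | 77.6% | 6.5 |
| 0.3, 0.4, 0.7 | 0.24 | 65.3% | 67.9% | 2.6 |
| 0.5, 0.35, 0.6 | 0.09 | 73.4% | 73.7% | 0.3 |

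Direct simulation of the adjusted CRR5 model agrees: gains run from about 0, through about 5 to 11 points at ρ 0.5 to 0.7 with equal SDs of 0.4, up to about 24 points at ρ = 0. The covariate never cost power in the settings tried. In mixtures with DGF of 50% v 35% it gained 1 to 9 points.

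**Imbalance.** If the arms differ in mean log baseline by k standard errors, the unadjusted CRR5 difference moves by about r·k of its own standard errors. With r = 0.48 and k = 2 this is 0.96. It averages to zero over randomisations but not within one trial.

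**The case against.** The strongest reply is that nothing is misstated. A two-sample t-test is valid under randomisation, and simulated type I error was about 5%. No power was promised for CRR5, and the article says that its statistics section is a summary with detail to follow in an SAP that is not shown. All of this stands, and it limits the point to efficiency on one secondary outcome. It does not remove the point, because the article does not leave the test open: it names it.

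A reader might infer more than the documents support, in four ways.

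- *That the loss is as large as 36 points.* A gap of that size appears only if the t-test on CRR5 is set against a regression of log day-5 creatinine on log baseline, at zero correlation between the two creatinines. That comparison changes the outcome scale and adds the covariate together. At (0.5, 0.35, 0.6), a t-test on the log ratio with no covariate already has 78.3%, against 73.4% for CRR5 and 79.1% for the full log model, so nearly all of that gain comes from the log scale.
- *That a low pretransplant creatinine always goes with a low CRR5.* The sign of r depends on ρ, s0 and s5, and it can be zero or negative, as shown above.
- *That log day-5 creatinine should replace CRR5.* That would change a named endpoint with a cited definition, and its advantage depends on the model. In illustrative mixtures at 50% v 35% DGF, the t-test on CRR5 had slightly more power than the log model (66.5% v 63.0%, and 63.5% v 60.3%).
- *That CRR2 has the same remedy.* Its day-1 reference is measured after randomisation and may be affected by treatment, so it is not a baseline covariate.

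**Conclusion.** The point holds as one of precision. CRR5 is tested without the baseline value that every CRR5 already requires, and precision is lost to the extent that the two remain correlated. The size is unknown from the documents. Under log-normal creatinine with 188 per arm, the covariate alone is worth about 0 points of power where CRR5 and baseline are nearly uncorrelated, about 5 to 11 points at ρ 0.5 to 0.7 with equal log SDs of 0.4, and up to about 24 points at ρ = 0. That upper end requires pretransplant and day-5 creatinine to be unrelated. Any further gain from a log scale is a separate matter. The stated test is not biased or invalid, and the DGF analysis and the 376 and 400 patients are unaffected.

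**What to change.** Under Secondary outcomes, separate CRR5 from CRR2. Compare CRR5 between arms with a linear model (ANCOVA) containing arm and pretransplant creatinine, preferably log-transformed, and report the adjusted mean difference with its 95% CI. Use the same pretransplant value that forms the CRR5 denominator. Leave the CRR2 comparison out of this change. A regression of log day-5 creatinine on arm and log pretransplant creatinine may be added as a sensitivity analysis, labelled as such.

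The cost is one sentence in the protocol or SAP. No new data are needed, and the endpoint and its definition stay as they are. The article says that the SAP will be written before the first interim analysis, so the change can be fixed there before that analysis.

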**Trial registration number:**

ISRCTN15821205; Pre-results.

Strengths and limitations of this studyThis is a large multicentre randomised controlled trial. It will provide evidence of the effect of ex vivo normothermic perfusion (EVNP) on early graft function in donation after circulatory death kidney transplantation.The secondary objectives will allow us to examine the impact of EVNP on rates of acute rejection and longer term graft function and survival.Tissue, blood and urine samples will enable a more in-depth analysis of the effects of EVNP on ischaemia reperfusion.The limitation of this study is the lack of blinding. Owing to the nature of the technique and in order to report safety outcomes, it is not possible to blind the surgical team to the allocation of the kidney.Delayed graft function, defined as dialysis within the first week of transplantation, is subjective. However, it is the best accepted measure of early graft function.

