### Randomisation

Patients will be allocated at random in a 1:1 ratio to either static cold storage (CS) plus 1 hour of EVNP (n=200) or CS (n=200) only. A patient information sheet will be given to potential recruits on admission for DCD kidney transplantation and written informed consent will then be obtained (see online supplementary appendices 1 and 2). Randomisation will be performed after the transplant recipient and kidney have both arrived in the transplanting centre and a final decision to proceed with transplantation has been made by a member of the study team. The randomisation will be performed on a web-based system (sealed envelope) which uses a computer-generated randomisation sequence. In cases where paired kidneys from the same donor are transplanted in the same centre, one kidney from the pair will be randomly allocated to CS and the other to EVNP. In these cases, the randomisation will also determine which kidney (right or left) will be transplanted first. Owing to the nature of the trial, no one is blinded to treatment allocation.

10.1136/bmjopen-2016-012237.supp1supplementary appendix

10.1136/bmjopen-2016-012237.supp2supplementary appendix

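### Adding donor age to the longitudinal creatinine and eGFR model would sharpen the between-arm differences at 1 to 12 months at no cost

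*Protocol article*

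**What the plan says.** The Protocol article names a method for later graft function. Under Secondary outcomes, creatinine and eGFR at the four follow-up visits will have "mean values compared using two-way analysis of variance with repeated measures for patients in each arm of the trial". The same paragraph adds: "Any difference between arms in the way serum creatinine and eGFR change over time will also be assessed using this model". The terms are therefore arm, time and their interaction, and no covariate is mentioned.

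Under Primary analysis, a few lines above, DGF will be compared with a "logistic regression model adjusting for cold ischaemic time and donor age". Nothing in the article carries either covariate over to the secondary outcomes.

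The strengths and limitations list after the abstract makes later function an aim of the trial: "The secondary objectives will allow us to examine the impact of EVNP on rates of acute rejection and longer term graft function and survival".

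**The concern.** The plan treats donor age as prognostic for early function but leaves it out of the model for later function of the same kidneys. Donor age is settled before randomisation, EVNP cannot alter it, and the primary model already requires it for every patient. In a linear model, a prognostic baseline variable that is omitted leaves its between-patient variance in the error term of the arm comparison. The confidence interval for each arm difference is then wider than it need be.

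What is at stake is precision on a stated secondary objective. The validity of the comparison, the primary analysis and the sample size are not affected.

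**Working it through.** **Number of patients.** The article gives no sample size for creatinine or eGFR; its only calculation is for DGF. It asks for "a total of 376 patients receiving a DCD kidney" to detect a fall from 50% to 35% "with a power of 80% and a statistical significance of α=0.05". With two-sided alpha (assumed, as sidedness is not stated), the usual two-proportion formula gives 170 per arm (340) without continuity correction and 183 per arm (366) with it. The latter is 2.7% below 376. The withdrawal step reproduces exactly: 376 / 0.94 = 400. I use 376 / 2 = 188 per arm below. The number fixes the scale, but the percentage changes do not depend on it.

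**Effect of adjustment.** Let rho be the within-arm correlation of donor age with the outcome at a visit. Adjusting for donor age multiplies the variance of the arm difference by (1 − rho²), so:

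- change in standard error = 1 − √(1 − rho²)
- power, for a contrast with 80% unadjusted power = Φ[(1.960 + 0.842) / √(1 − rho²) − 1.960]
- equivalent unadjusted total = 376 / (1 − rho²)

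The contrast with 80% unadjusted power at 188 per arm is 2.802 × √(2/188) = 0.289 SD. Both rho and the 80% starting point are assumptions; the article gives neither for creatinine or eGFR.

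| rho (assumed) | Variance removed | SE reduction | Power from 80% | Equivalent N |
|---|---|---|---|---|
| 0.1 | 1% | 0.5% | 80.4% | 380 |
| 0.2 | 4% | 2.0% | 81.6% | 392 |
| 0.3 | 9% | 4.6% | 83.6% | 413 |
| 0.4 | 16% | 8.3% | 86.4% | 448 |
| 0.5 | 25% | 13.4% | 89.9% | 501 |

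Example at rho 0.3: √0.91 = 0.954; 2.802 / 0.954 = 2.937; 2.937 − 1.960 = 0.977; Φ(0.977) = 0.836. The gain reaches about five points only at rho near 0.35 (84.9%).

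**Chance imbalance in donor age.** This is the same variance seen from another side. Assume a donor-age SD of 15 years and a loss of 0.5 mL/min of eGFR per donor year. The arm difference in mean donor age then has standard error 15 × √(2/188) = 1.55 years, which is 0.77 mL/min. This is a component of the unadjusted standard error, and components combine as squares. With an assumed eGFR SD of 15 to 25 mL/min:

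- unadjusted SE: 15 × √(2/188) = 1.55, up to 25 × √(2/188) = 2.58
- adjusted SE: √(1.55² − 0.77²) = 1.34, up to √(2.58² − 0.77²) = 2.46
- narrowing: 0.21 down to 0.12 mL/min

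These two cases have rho = 7.5/15 = 0.5 and 7.5/25 = 0.3, so they are the 13% and 5% rows of the table in other units.

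**Split pairs.** Under Randomisation, two kidneys from one donor transplanted in the same centre go to opposite arms, so donor age is exactly balanced within each pair. The article does not give the share of such kidneys. If it were half (assumed), only 94 per arm could be imbalanced: 15 × √(2 × 94) / 188 = 1.09 years, or about 0.55 mL/min instead of 0.77.

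**Arm-by-time term.** This is a contrast of changes within patients. A donor-age effect that is constant over visits cancels from it, so a donor-age main effect leaves its precision unchanged.

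**The case against.** The strongest reply is that the article says its analysis section is a summary and that a full SAP will follow, so a covariate list for one secondary outcome belongs there. That would settle the matter if the article had left the method open. It names one, and in the same summary it lists covariates where adjustment is intended. The natural reading is an unadjusted model. The unseen SAP may already add donor age, in which case nothing more is needed.

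A second reply is that nothing here is wrong: an unadjusted comparison of randomised arms is unbiased, and the article compares its other secondary outcomes with simple tests throughout. This stands. A reader might infer from the two models side by side that the plan contradicts itself or that the longitudinal comparison is biased. The documents support neither; adjusting only the primary outcome is a coherent choice, though less efficient here.

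A third reply is that the gain rests on assumption. This also stands. The article supports donor age as a covariate for DGF only and powers nothing on eGFR. At a correlation of 0.1 or 0.2 the gain is slight.

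Two further inferences should be resisted. One is that chance donor-age imbalance is a separate harm that adds about 0.8 mL/min to the standard error. It is already part of that standard error, and the split pairs reduce it. The other is that donor age is the only baseline measure of kidney quality: the Renal fibrosis section also plans pretransplant biopsies with quantified fibrosis. The case for donor age is that the primary model already needs it.

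**Conclusion.** This is a free improvement, not an error. The longitudinal creatinine and eGFR comparison is valid as planned but gives up precision on the between-arm differences by omitting a pre-randomisation variable that the primary model already uses. Over assumed correlations of 0.1 to 0.5, the standard error would fall by 0.5% to 13%, and a contrast with a hypothetical 80% power would rise to between 80.4% and 89.9%. The upper end should not be read as a known loss, because no figure in the article fixes the correlation. The benefit is confined to the arm differences; the arm-by-time test and the planned sample size of 376 (400 recruited) stay as they are.

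**What to change.** In the Secondary outcomes section, or in the SAP that the article promises before the first interim analysis, add donor age as a continuous covariate to the longitudinal models for creatinine and eGFR, alongside arm, time and arm-by-time. Report the donor-age-adjusted arm difference at 1, 3, 6 and 12 months with 95% confidence intervals.

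Do not add total cold ischaemic time to this model. Randomisation takes place after the kidney reaches the transplanting centre, so cold time is still accruing and could depend on the allocated arm.

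The cost is one line of wording. Donor age is already needed for the primary model, so no extra data, patients or staff are required.
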